### Quantitative instruments

2.5.

In line with the theoretical five-domain structure applied by this study, we will choose a multidimensional assessment strategy to cover the different domains of PL. Due to acceptable measurement characteristics, the second version of the Canadian Assessment of Physical Literacy (CAPL-2) (84, 85), the Canadian Passport for Life (PFL) (86), or the Canadian Physical Literacy Assessment for Youth (PLAY) (87) were taken into account (88), all measuring the cognitive, psychological/affective, and physical domains of PL. As another alternative, the Physical Literacy in Children Questionnaire (PL-C Quest) will be selected as an opportunity for evaluation (89). Based on the Australian understanding of PL, the PL-C Quest is a picture-based self-assessment of the physical, psychological (affective), cognitive, and social domains. Available data from factor analyses indicate a good model fit for boys in the English-speaking setting (90). In detail, the psychometric properties of the procedure are reported as moderate (social domain) to good (physical domain), with model fit being better for boys than for girls. Additionally, the image-based method can be beneficial for children with language or comprehension difficulties. In the present study, we will consistently draw on the “summer items” (e.g., skateboarding instead of skating and safe swimming in the sea instead of safe tobogganing on the slopes) of the available item pool of the PL C Quest. A more detailed overview is given in Table 2.

**Table 2 T2:** A detailed overview of the quantitative assessments in regard to the PL domains.

	Physical domain	Cognitive domain	Psychological (affective) domain	Social domain	Behavioral domain
Pilot study 1 [uncontrolled pre-post design]	PL-C Quest [12 items]	PL-C Quest [7 items] CAPL-2 [5 items]	PL-C Quest [7 items] CAPL-2 [12 items]	PL-C Quest [4 items]	CAPL-2 [1 item]
Pilot study 2 [uncontrolled pre-post design]	PL-C Quest [12 items]	PL-C Quest [7 items] PFL [3 items] PLAYself [2 items]	CAPL-2 [6 items] PL-C Quest[7 items]	PL-C Quest [4 items]	CAPL-2 [1 item]
Main study [controlled design]	DMT 6–18 [8 tests] PL-C Quest [12 items]	Selection based on data from the pilot studies	Selection based on data from the pilot studies	PL-C Quest [4 items]	CAPL-2 [1 item]

CAPL-2, Canadian assessment of physical literacy, second version; DMT, Deutscher Motoriktest; PFL, passport for life; PL-C Quest, physical literacy in children questionnaire.

#### Physical domain

2.5.1.

In the pilot studies, the physical domain will be evaluated using the PL-C Quest (89) and, therefore, a self-assessment procedure. The children are asked to inspect 12 pairs of pictures on different topics (e.g., object manipulation, flexibility, or coordination) and to assign themselves to the picture with the most suitable description. For the main study, we will employ a complementary objective measure of physical competence to map children's development. The assessment will be based on the International Physical Performance Test Profile 6–18 (Deutscher Motorik Test, DMT 6–18) to operationalize this domain (91). This procedure offers the advantage of having age-group and gender-specific norm values.

#### Cognitive domain

2.5.2.

Within the scope of pilot study 1, the assessment of this knowledge and comprehension domain will be collected via seven picture-based items of the PL-C Quest (e.g., rules, anticipation, awareness) (46). Similar as to the physical domain, children assign themselves to the picture with the most suitable description. Additionally, specific knowledge questions of the CAPL-2 are used (e.g., cloze test or multiple-choice questions) (84, 85). Since the scientific community has reported problems with the assessment of the cognitive domain (88, 92, 93), the second pilot study will employ an additional survey for the cognitive domain. For this purpose, we will use the items of the living skills scale of the PFL (86), labelled as *thinking* (exemplary item: “I can use words like run, hop, skip and dodge to explain how I move”), combined with supplementary questions of the PLAYself (exemplary items: “I understand the words that coaches and PE teachers use”) (87). Following the two pilot studies, a decision will be made as to which method is best suited to map the cognitive component.

#### Psychological (affective) domain

2.5.3.

We will record the psychological domain based on seven pairs of images of the PL-C Quest, which illustrate topics like collaboration or dealing with failure. In addition, we will record the affective domain via the CAPL-2, including its subcategories intrinsic motivation, PA competence, predilection, and adequacy (84, 85). Each of these subcategories will be evaluated by a 4-point Likert scale (predilection and adequacy) and a 5-point Likert scale (intrinsic motivation and PA competence), respectively. The answer selection in the Likert scale will be transferred into a score (0.5 or 0.6 points for the lowest PL expression and 2.5 points for the highest PL expression per question), which will result in a total score for this domain. This score will be interpreted by using norm values of the CAPL-2 (85). To subsequently reduce the complexity of the questionnaire, we will survey only the subscales “intrinsic motivation” and “PA competence” in the second pilot study. These two subscales will be selected because they play a particular role in the definition of PL and can be seen as drivers of enduring physical activity (75). Following the comparative evaluation of the two pilot studies, we will make a final decision as to which items are used to survey the psychological domain.

#### Social domain

2.5.4.

The social domain is collected solely via the PL-C Quest (89). The four pairs of images represent the components of relationships, collaboration, ethics, as well as society and culture. It should be emphasized here that the reliability of this subscale was described as only moderate in the initial sample of Barnett and colleagues. Since other evaluation procedures [e.g., the CAPL-2 (85)] do not measure the social domain, this scale is used despite its psychometric weakness and without further scale to validate the measurement.

#### Behavioral domain

2.5.5.

In the pilot study, the participating children will be invited to indicate leisure-time sports and the number of days within a week with a daily PA level above the WHO recommendation of 60 min. The number of days corresponds to the CAPL-2 survey (85).

#### Further participant characteristics

2.5.6.

In addition, we will acquire the following information from the participating children via self-report: gender, age (via birthday date), body mass index (via height and weight), and sport club membership, their potential participation in recreational sports outside school and how the children manage their way to school (actively by foot, bike, scooter or passively by car or public transport).

### Sample size

2.6.

We performed sample size calculations with the software G*Power version 3.1 (94). For the uncontrolled *pilot study* adopting a pre-post character, we expect a minimum effect size of *d_z_* = 0.40 while considering the influence of general development effects. In this case, the minimum sample size to be acquired through one-sided, paired sample *t* tests (statistical power ≥ 80% and one-sided *p* < .05) will be *n* = 41. Assuming a conservative dropout rate of 25% (as usual for this target group, see (14, 95), an initial sample of *n* = 55 children will be recruited. Given an average number of approximately 20 pupils per class, we will include three to four classes for the pilot study.

For the subsequent main study in a control group design, we base a significant effect on time-group interactions of repeated multivariate analyses of variance (MANOVA). Aiming to control for general development effects through the involvement of a control arm, we set a smaller effect size of *d* = 0.30 (corresponding to *f* = 0.15) in this part of the study. Power calculations with an adjusted significance level (five PL outcomes:.05/5) of *p* ≤ .01 resulted in a required sample size of *n* = 134 children across the two study conditions (autoregressive pre-post correlation *r_t_* = 0.50, statistical power ≥ 80%). A total of nine to ten classes (dropout corrected *n* = 179 children) should initially participate in the main study.

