### Research questions, goals, and hypotheses

1.3.

The main goal of the present study is to investigate the effectiveness of a PL intervention in different schools in the city and city state of Bremen, Germany. This study addresses the following primary research question: *Can an intervention with clear foundations in the integrated PL domains systematically promote PL among children 8–11 years of age?* Accordingly, we will test the main hypothesis (one-sided procedure) that children in the intervention condition develop significantly better over the interventional period in PL outcomes compared to children in the control condition.

In addition, the present study pursues two sub-goals on its way toward the primary goal: (a) to derive holistic, age-specific intervention components for 8–11 years old children with explicit manifestations in the PL concept, and (b) to implement the intervention in cooperation with primary schools in the city and city state of Bremen, Germany. In case of a successful implementation and evaluation (i.e., approval of the research question), the present study also reserves capacities for potentially preparing the dissemination of the intervention concept.

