**Figure 1 F1:**
[figure not shown]
Study design.

After the completion of the two pilot studies, we will follow up with the main study. The main study will more rigorously examine the effectiveness of the final PL intervention in a controlled design. In each school, an even number of classes of one grade level will participate in the study. Half of the classes will be assigned to the intervention condition, which will pass regular half-year education in primary school plus a weekly PL intervention. In contrast, the other half of the classes will be assigned to the control condition, which will undergo only regular half-year education in primary school without the additional PL intervention (see Figure 1). Randomization cannot be fully realized as pragmatic reasons co-influence the assignment to the different intervention arms (57). The main study, which also includes two measurement time points (e.g., pre and post), will take place between September 2023 and February 2024. In summary, the research design with two pilot cycles (51) accounts for potential pitfalls (e.g., revision of PL content) toward a sound examination of the effectiveness of the PL intervention. The final reporting of study will adhere to the recent physical literacy interventions reporting template suggesting a total of 14 items (58). The ethics committee of the University of Oldenburg, Germany, has approved the conduction of the study (sign Drs.EK/2022/057).

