#### Quantitative analysis

2.7.2.

The *pilot study* using a non-controlled pre-post design will be analyzed with paired sample tests. In this case, the time (pretest vs. posttest) will be treated as the independent variable and the PL domains as the dependent variables. Depending on the support or rejection of normal distribution (based on Kolmogorov Smirnov test), we will compute paired sample *t* tests or Wilcoxon tests for the inferential statistical comparison.

Furthermore, the Transparent Reporting of Evaluation with Non-Randomized Designs (TREND) statement will serve as an overarching framework (99) to guide the design, evaluation, and reporting of the *main study*. We will use a variance analytical design with multivariate character to quantitatively examine the effectiveness of the intervention arm in comparison to the control arm (repeated MANOVA). Statistically, main attention will be paid to the time-group interaction in the repeated MANOVA (within-subjects factor: time; between-subjects factor: group condition). We will determine the magnitude of the intervention effect on the eta square (*η*^2^) coefficient by adhering to the interpretation guidelines as suggested by Cohen (100). Despite the nested structure of data (e.g., classes as clusters), multilevel analysis (i.e., linear mixed methods) cannot be realized owing to the low number of second-order units (*N* ≤ 10 schools). Even robust methods, like the Kenward-Roger correction, require a larger number of clusters for adequate calculations (101). To account for potential clustering at the class level, we will enter the class as covariate within the MANOVA. Missing data in the longitudinal data set will be imputed with the expectation maximization (EM) algorithm (102). Nevertheless, we will withdraw children from the analysis who did not attend (a) the first session with the baseline measurement and (b) at least eleven of the 14 sessions (<75%; i.e., exclusion of those who were missing more than three sessions of the PL intervention).

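### The main study's n = 134 gives 80% power for a 0.60 SD difference in change between arms; for the stated d = 0.30, power is about 19% per outcome

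*Protocol article*

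**What the plan says.** Section 2.6 (Sample size) of the protocol article names the test that drives the main-study sample size: "we base a significant effect on time-group interactions of repeated multivariate analyses of variance (MANOVA"). Because a control arm is meant to remove general developmental gains, the section chooses an effect below the pilot's dz = 0.40, namely an "effect size of *d* = 0.30 (corresponding to *f* = 0.15"). Alpha is divided over the five outcome domains: "Power calculations with an adjusted significance level (five PL outcomes:.05/5) of *p* ≤ .01". With a pre-post correlation of 0.50 and power of at least 80%, the result is a "required sample size of *n* = 134 children across the two study conditions", raised to 179 for dropout.

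The rest of the article agrees on the design. Section 2.1 (Study design) says "The main study, which also includes two measurement time points (e.g., pre and post"), with half of the classes in each condition. Section 2.7.2 (Quantitative analysis) confirms the test: "Statistically, main attention will be paid to the time-group interaction in the repeated MANOVA". Section 1.3 adds that "we will test the main hypothesis (one-sided procedure"). The article does not define d further.

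**The concern.** Halving d to obtain f is correct when two group means are compared once. The effect tested here is an interaction in a 2 x 2 layout. There, a given difference in change between arms is spread over four cells and yields an f half as large as in the single comparison. Entering f = 0.15 as an interaction effect therefore sizes the study for an effect twice the one written down.

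This matters because the abstract says the results will decide whether the intervention is scaled up, and section 3.3 ties dissemination to a successful main study. If the true effect is the stated 0.30 SD, each outcome has roughly a four-in-five chance of missing significance at alpha 0.01. A reader told that power was 80% could take such a result as evidence against an effect of that size.

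**Working it through.** **Inputs** (sections 2.1 and 2.6): k = 2 arms with equal allocation, m = 2 measurements, r = 0.50, alpha = 0.05/5 = 0.01, target power 80%, f = 0.15, stated N = 134.

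**1. Reproduce the stated n.** For the repeated-measures within-between interaction, the noncentrality is lambda = f² × N × m/(1 − r), with 1 and N − 2 degrees of freedom.
- With f = 0.15: lambda = 0.0225 × N × 2/0.5 = 0.09N.
- N = 132: power 0.796. N = 134: lambda = 12.06, power 0.803.

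So 134 is the smallest even N reaching 80%, which matches the article. Other settings do not match: alpha 0.05 gives 90, one-sided 0.01 (the F test at 0.02) gives 116, and the between-subjects formula on the same inputs gives 394.

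**2. What f = 0.15 means for this test.** Take cell means in SD units: control 0 and 0, intervention 0 and δ. After removing the arm and time main effects, each of the four interaction effects is ±δ/4. Hence f = δ/4.
- f = 0.15 gives δ = 4 × 0.15 = 0.60 SD.
- δ = 0.30 gives f = 0.30/4 = 0.075.

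**3. Cross-check on change scores.** With two time points the interaction is the two-sample comparison of pre-post change. The SD of change is √(2(1 − r)) = √(2 × 0.5) = 1 score SD, so ncp² = δ² × N/4. Setting δ² × N/4 = 0.09N gives δ² = 0.36 and δ = 0.60. Because the SD of change equals the SD of the score at r = 0.50, it makes no difference which of the two standardises d.

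**4. Power at the stated effect.** With f = 0.075 and N = 134, lambda = 0.005625 × 134 × 4 = 3.015.

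| Setting (d = 0.30, r = 0.50 unless stated) | Power |
|---|---|
| F test, alpha 0.01, N = 134 | 19.5% (simulation 19.2%) |
| One-sided 0.01, N = 134 | 27% |
| F test, alpha 0.05 (no correction), N = 134 | 41% |
| One-sided 0.05 (no correction), N = 134 | 53% |
| F test, alpha 0.01, all 179 retained | 28% |
| ANCOVA on the post value, two-sided 0.01, N = 134 (normal approximation) | 28% |
| F test, alpha 0.01, r = 0.70, N = 134 | 36% |

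**5. What 80% would take.** At alpha 0.01 and r = 0.50, N = 524 (power 0.801; N = 522 gives 0.7996), or 524/0.75 = 699 after the same 25% dropout allowance. Keeping N = 134 would need r of about 0.875 instead of 0.50.

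**6. Consistency with the stated rationale.** The section intends an effect smaller than the pilot's dz = 0.40. The effect for which 134 gives 80% power is 0.60 SD of change, which is larger. At a difference of 0.40 SD, power with 134 children is 39%.

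**The case against.** The best defence is that d is never defined, that f rather than d was the power input, and that 134 is correct for f = 0.15. On that view the fault is a mislabelled effect size, not a wrong n. This is fair as a description of where the error sits, but it does not rescue the power claim. For a time-by-group interaction, the natural meaning of d is the between-arm difference in change. The pair d = 0.30 and f = 0.15 would agree for a group main effect, or if the arms moved 0.30 SD in opposite directions. The article says neither, and the second fits poorly with using the control arm to absorb normal development.

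Reproducing 134 does not by itself prove which effect was entered: the time main-effect test has the same noncentrality and degrees of freedom in this design. The identification rests on section 2.6 naming the interaction, which it does plainly.

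The 19% is power for one outcome at alpha 0.01, whereas the analysis is a multivariate test. If all five outcomes shifted by 0.30 SD, a joint test at alpha 0.05 would have about 85% power with uncorrelated change scores, 47% at correlation 0.3 and 35% at 0.5. These correlations are assumptions; the article gives none. Since section 2.6 divides alpha by five, the per-outcome figure is the one comparable with its claim, and domains of one construct are likely to be positively correlated.

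The one-sided hypothesis raises 19% to 27%. That stands, and the range should be quoted, but it remains far below 80%. It also sits uneasily with the stated n, which comes from the F test at 0.01.

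Finally, the article does not say how a non-significant result would be read, so the risk of misreading is conditional.

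**Conclusion.** The concern holds. The sample size of 134 is right for f = 0.15, but f = 0.15 is a between-arm difference in change of 0.60 SD, not 0.30. For d = 0.30, per-outcome power at alpha 0.01 is about 19% with the F test that produces 134, or 27% one-sided, against the stated 80% or more. The stated n is about a quarter of the 524 needed (134/524 = 0.26).

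This rests on reading d as the difference in pre-post change in SD units, on equal arms, and on the article's own r = 0.50. It takes no account of clustering by class, which would lower power further. Because the stated power bears on the scale-up decision, it must be corrected.

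**What to change.** Correct section 2.6 in one of two ways:

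- State that 134 children give 80% power, per outcome at alpha 0.01, for a between-arm difference in pre-post change of 0.60 SD (f = 0.15), and drop the equation with d = 0.30.
- Or keep d = 0.30, give it as f = 0.075, and state that power at 134 is about 19% at alpha 0.01 (27% if the test is one-sided).

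In either case define d explicitly and say whether the calculation is one- or two-sided. State that non-significance will not be taken as evidence against an effect of 0.30 SD. Presenting the main-study results chiefly as estimates with confidence intervals would serve this well, though correcting the power statement does not depend on it.

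The cost is wording in the sample size section and a less favourable stated power. The number of classes and children need not change.

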**Methods:**

The physical literacy intervention cultivates explicit theory-content links and comprises 12 heterogeneous sessions (each 60-90 min in length). The study contains three different phases with two initial pilot studies and a subsequent main study. The two pilot studies take a mixed-methods character by drawing on quantitative pre-post-designs as well as interviews with children (in groups). In the main study, we will longitudinally compare the course of PL values (five outcome domains: physical, affective, cognitive, social, behavioral) between two study arms: school classes of children are either assigned to an intervention condition (regular physical education and health care plus PL intervention) or to a control condition (regular physical education and health care only).

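### Splitting the 5% error rate flatly over five domains (0.01 each) gives up power that Holm's step-down rule would return at the same error rate and the same n

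*Protocol article*

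**What the plan says.** The main hypothesis (1.3) is that "children in the intervention condition develop significantly better over the interventional period in PL outcomes compared to children in the control condition". The abstract lists the outcomes as "five outcome domains: physical, affective, cognitive, social, behavioral".

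Section 2.6 sizes the main study on the interaction of time and group, with the error rate divided by five: "Power calculations with an adjusted significance level (five PL outcomes:.05/5"), that is p ≤ .01 for each outcome. The other inputs are d = 0.30 ("corresponding to *f* = 0.15") and "autoregressive pre-post correlation *r_t_* = 0.50, statistical power ≥ 80"%. The result is a "required sample size of *n* = 134 children across the two study conditions", or 179 after dropout.

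Section 2.7.2 plans a repeated MANOVA with attention on the same interaction. It gives no threshold for the individual domains and no multiplicity procedure. The equal split in 2.6 is therefore the only rule in the article for sharing the 5%.

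**The concern.** Under an equal split, each domain must reach p ≤ .01 whatever the other four show. That wastes most when several effects are real, because once one domain is declared significant, fewer hypotheses remain to be protected and the threshold can be relaxed without raising the family-wise error. Section 2.3.1 links every session to the physical, cognitive, affective and social domains and delivers all sessions through actual movement (the behavioural domain). Effects in several domains are thus what the programme aims for.

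At stake is the chance of showing a real effect in each domain, and above all in several together. The article says the results will inform a decision on scale-up, and its message is an integrated effect rather than one in a single domain.

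**Working it through.** **Inputs from the article.** f = 0.15, r = 0.50, two measurement times, 0.05/5 = 0.01 per outcome and power of at least 80% (all 2.6). Allocation is half and half by class: "Half of the classes will be assigned to the intervention condition" (2.1). The correlation between the five domains is not given, so it is assumed to be 0, 0.3, 0.5 or 0.7.

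**1. Reproduce the stated n.** For the interaction of two groups and two times, λ = f² · N · 2/(1 − r) = 0.0225 · N · 4 = 0.09N. With N = 134, λ = 12.06 on F(1, 132). At α = 0.01 the power is 0.803; N = 133 gives 0.7996. So 134 is the smallest N that reaches 80%. Dropout at the 25% stated for the pilot gives 134/0.75 = 178.7, rounded up to 179. Both figures match.

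The hypothesis is stated as directional ("we will test the main hypothesis (one-sided procedure"), but 134 matches the ordinary two-sided F test; one-sided 0.01 would give N = 115. This does not affect the comparison below, because Holm shares the error rate in the same way for either direction.

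**2. Thresholds.** Bonferroni uses 0.01 five times. Holm orders the p-values and uses 0.05/5, 0.05/4, 0.05/3, 0.05/2 and 0.05, stopping at the first failure. Single-test power at N = 134 is:

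| Level | 0.01 | 0.0125 | 0.0167 | 0.025 | 0.05 |
|---|---|---|---|---|---|
| Power | 80.3% | 82.5% | 85.1% | 88.5% | 93.2% |

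**3. Why the error rate is unchanged.** Suppose m₀ domains have no effect. When Holm first rejects one of them, at least m₀ hypotheses are still in play, so the threshold used is at most 0.05/m₀. The chance that any of the m₀ p-values falls below that is at most m₀ · 0.05/m₀ = 0.05, whatever their dependence. Holm's first threshold is 0.01 and later ones are larger, so every Bonferroni rejection is kept.

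**4. Size of the gain.** Simulation with 400,000 replicates per scenario: five two-sided t tests with 132 df, equal correlation 0 to 0.7, and noncentrality √12.06 = 3.47 in each responding domain. Ranges run over the correlations.

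| Domains responding | Power per domain: Bonferroni | Holm | All responding domains significant: Bonferroni | Holm |
|---|---|---|---|---|
| 5 | 80% | 88–91% | 33–59% | 68–80% |
| 4 | 80% | 85–87% | 42–62% | 61–75% |
| 3 | 80% | 83–84% | 52–66% | 62–73% |
| 2 | 80% | 82% | 64–71% | 68–74% |
| 1 | 80% | 80% | 80% | 80% |

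Holm's simulated family-wise error was at most 4.9% in every scenario. With independent tests and no effects, arithmetic gives 1 − 0.99⁵ = 4.9%.

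**5. Half the effect.** With noncentrality 3.47/2 = 1.74 and correlations 0 to 0.5, power per domain goes from 19% to 22–24% with five responding domains and from 19% to 20–21% with three.

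**6. What does not change.** The chance of at least one significant responding domain is practically the same, because Holm's first step is also 0.01. With three responding domains and correlation 0.5 it is 95.2% under Bonferroni and 95.3% under Holm.

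**The case against.** The strongest reply is that nothing here is wrong. Bonferroni is valid, n = 134 is right for it, and 0.05/5 appears only in the power calculation. Planning at 0.01 is also how one would plan conservatively for Holm. This stands in part: the point is one of efficiency, and n should not change. But 2.6 does state an equal split, and nothing elsewhere in the article replaces it. If 0.01 is only a planning level, the article gives no decision rule for the five outcomes, and the same sentence supplies one.

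Second, the largest gains need all five domains to respond at f = 0.15. The behavioural domain is a single self-report item, and the article admits the social scale is psychometrically weak, so equal effects are doubtful. The effect may also be smaller. If d = 0.30 means a difference in change of 0.30 SD, then with r = 0.50 the SD of change is √(2(1 − 0.50)) = 1 SD and the noncentrality is 0.30 · √(67/2) = 1.74. That is the half-effect case, where the gain is small. All of this stands as a limit on size; none of it gives a case where Holm rejects less.

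Third, the named analysis is a repeated MANOVA. If domain tests were carried out only after a significant omnibus test, the power figures would need recomputing. Clustering by class would also lower power under both rules. Both are true, but neither alters the ordering of the two rules.

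Fourth, the hypothesis does not require all five domains to be significant, and the chance of at least one is practically unchanged. That is correct. The benefit lies in claims about the second and later domains.

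**Conclusion.** The concern holds. As a decision rule, Holm rejects everything the flat split rejects, at the same 5% family-wise error and the same n. At the planned f = 0.15 with all five domains responding, power per domain rises from 80% to 88–91%, and the chance of showing all five rises from 33–59% to 68–80%. With three responding domains the gain per domain is 3 to 4 percentage points. With one it is practically nil, and at half the effect it is a few points at most.

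These figures rest on independent children (as in the article's own calculation), equal effects in the responding domains, assumed correlations of 0 to 0.7 (0 to 0.5 at half the effect), and domain tests not gated by the MANOVA. The plan contains no error on this point; it forgoes a gain that costs almost nothing.

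**What to change.** Keep n = 134 at α = 0.01 as the conservative planning case; it should not be reduced on this ground. In 2.6 and 2.7.2, state: *The five domain-specific tests of the time-by-group interaction are judged by Holm's step-down procedure (thresholds .05/5, .05/4, .05/3, .05/2, .05) at a family-wise error rate of 5%.* Fix this before any main-study outcome data are examined, so that the choice cannot look data-driven.

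The cost is one sentence, with no additional children or measurements. The one drawback is that simple simultaneous confidence intervals remain at the Bonferroni level (99% per domain), so a domain declared significant at a later Holm step may have an interval that includes zero. A short note in the report can explain this.

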The focus of the PL interventions will be placed on pupils of the third or fourth grade, wherein the class will serve as the level for the assignment to study conditions. Accordingly, the present study will address children aged between 8 and 11 years within the trial and analyses. Furthermore, children and their legal guardians will have to provide informed consent to study participation. In line with the inclusive potential of PL (69), children with diagnosed special needs will be invited to join the intervention (as long as they can participate in regular physical education) and evaluation. Nevertheless, they will be excluded from the analysis for psychometric reasons.

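### Section 2.6 claims at least 80% power as if 134 children were independent, although whole classes are assigned and only nine to ten take part

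*Protocol article*

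**What the plan says.** Section 2.6 bases the main-study sample size on the time-by-group interaction of a repeated MANOVA. The inputs are an effect size ("we set a smaller effect size of *d* = 0.30 (corresponding to *f* = 0.15"), an "adjusted significance level (five PL outcomes:.05/5) of *p* ≤ .01", and "autoregressive pre-post correlation *r_t_* = 0.50, statistical power ≥ 80"%. The result is 134 children in total, inflated for dropout and turned into classes: "A total of nine to ten classes (dropout corrected *n* = 179 children) should initially participate in the main study".

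The design is described elsewhere as follows.
- **Unit of assignment (section 2.2):** pupils are in grade three or four, "wherein the class will serve as the level for the assignment to study conditions".
- **Class count (section 2.1):** "In each school, an even number of classes of one grade level will participate in the study", with half of the classes going to each condition.
- **Sidedness (section 1.3):** "we will test the main hypothesis (one-sided procedure").
- **Analysis (section 2.7.2):** "Despite the nested structure of data (e.g., classes as clusters"), multilevel analysis is ruled out because there are too few higher-level units, and class is entered as a covariate.

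Section 2.6 contains no ICC, design effect or other cluster term.

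**The concern.** When whole classes are assigned, children in the same class share a teacher, a timetable and, in the intervention arm, a delivery group. Their changes are likely to be correlated, so 134 children carry less information about the arm contrast than 134 independent children. The number of classes, not of children, also limits how well the between-class variance can be estimated. A power figure that ignores both is too high for this design.

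The article says the results will inform whether the intervention is scaled up. A null result read as coming from a study with 80% power would be given more weight than the design can support.

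Section 2.7.2 does not repair this. Each class lies wholly in one condition, so class entered as a factor is confounded with the group effect. Entered as a single numeric covariate, it does not model clustering. In neither form does it feed into the sample size.

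**Working it through.** **1. Inputs.** From section 2.6: f = 0.15, r = 0.50, alpha = 0.01, 134 children, two measurement times. The 25% dropout and about 20 pupils per class are stated there for the pilot. The dropout is evidently reused, since 134/0.75 = 178.7, rounded up to 179. I take f = 0.15 as entered; whether it matches d = 0.30 is a separate question.

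**2. Reproducing the plan's figure.** For the within-between interaction, λ = f² × N × 2/(1 − r), with 1 and N − 2 degrees of freedom (df).
- N = 134: λ = 0.0225 × 134 × 4 = 12.06, power 0.803.
- N = 132: power 0.796.

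So 134 is the smallest even N reaching 80%. It is a two-sided 0.01 calculation with independent children; one-sided 0.01 would have given 116.

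**3. Adding the class structure.** Ten classes with 134 analysed children average 13.4 per class. The design effect is DE = 1 + (13.4 − 1) × ICC, and λ becomes 12.06/DE. The ICC is that of the pre-post change. It is not in the article, so the range is my assumption.

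| ICC | DE | Effective N | Power, 132 df | Power, 8 df |
|---|---|---|---|---|
| 0 | 1.00 | 134 | 80% | 57% |
| 0.01 | 1.12 | 119 | 74% | 51% |
| 0.02 | 1.25 | 107 | 69% | 46% |
| 0.05 | 1.62 | 83 | 55% | 35% |
| 0.10 | 2.24 | 60 | 39% | 24% |

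The two columns separate two effects. The 132 df column shows the design effect alone. The first row shows the df alone: moving from 132 to 8 df costs 23 percentage points before any ICC is assumed. The 8 df are ten classes minus two arms.

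**4. Sidedness.** At one-sided 0.01 with the same noncentrality, child-level power is 82%, 77%, 65% and 49% at ICC 0.01, 0.02, 0.05 and 0.10. With 8 df it is 71% at ICC 0, falling to 35% at ICC 0.10.

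**5. Class count.** A sum of even numbers is even, so nine classes cannot satisfy section 2.1. Section 2.2 requires consent from child and guardian, and excludes children with special needs from the analysis, but 179/20 = 8.95 carries no term for either. To reach 134 analysed children after 25% dropout, ten classes of about 20 need 134/(200 × 0.75) = 89% participation.

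**The case against.** **The arithmetic is not wrong.** This is true. 134 and 179 both reproduce. The defect is an omitted design feature, not a miscalculation.

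**The loss rests on an assumed ICC and on choices of sidedness and df.** This stands in part. At ICC 0.01 with child-level df the loss is modest (80% to 74%), and a one-sided reading of section 1.3 would bring it back to 82%. That is the only cell among the non-zero ICCs above 80%. The 8 df column describes a class-level test that section 2.7.2 does not specify, so it shows what the number of classes supports, not the power of the planned MANOVA.

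**Classes are split within each school.** This is a fair point. Differences between schools largely cancel from the arm contrast, so the relevant ICC is that between classes within schools, which argues for looking at the lower values as well. The df would also change, to fewer than 8 if school terms are fitted.

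**The plan already acknowledges nesting.** It does so in section 2.7.2, and the limitations section concedes that classes are few. Readers are not left unaware of clustering, but the power statement is unchanged by it.

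**A reader might infer that the class count assumes every pupil consents.** The article does not support that. It states no consent rate. Near-full participation (134/(180 × 0.75) = 99%) is needed only at nine classes, the count that section 2.1 already rules out. Ten classes need about 89%, and the class size of 20 is approximate and stated for the pilot.

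**Conclusion.** The power statement is wrong as written. The 80% holds only if children in the same class are independent and the test uses child-level df. For 134 analysed children in ten classes at two-sided 0.01, power is about 74% to 39% over assumed ICCs of 0.01 to 0.10 with child-level df, and 51% to 24% with 8 df. At one-sided 0.01 it exceeds 80% only at ICC 0.01 or below with child-level df, and is at most 71% with 8 df. With class-level df the shortfall therefore does not depend on the assumed ICC; with child-level df its size does.

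These figures take f = 0.15 as entered, equal class sizes and 134 children actually analysed. They do not show that any one power value is the true one.

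The conflict between nine classes and the even-number rule is real but minor. The participation point goes no further than this: section 2.6 makes no explicit allowance for non-consent or special-needs exclusions.

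**What to change.** In section 2.6, replace the unconditional statement of at least 80% power by the power for the planned number of classes over a stated range of ICCs for the pre-post change, between classes within schools (for example 0.01 to 0.10). Name the sidedness and the df used, and make the sidedness agree with section 1.3.

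As minor edits in the same section, change the class count to an even number so that it agrees with section 2.1. Add a sentence saying that the count makes no explicit allowance for non-consent or special-needs exclusions, with the participation it needs (about 89% for ten classes of about 20 at 25% dropout).

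The cost is a rewording of one section and a less favourable stated power. No extra enrolment is needed.
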